## Abstract

**Introduction:**

As the role of (neuro)inflammation in depression pathophysiology is emerging, augmentation of antidepressant treatments with anti-inflammatory drugs have shown beneficial results, but not consistently across all studies. Inconsistencies may be due to depression biological and clinical heterogeneity. Immuno-Metabolic Depression (IMD) has been put forward as a form of depression characterized by the clustering of low-grade inflammation, metabolic dysregulations and atypical, energy-related symptoms (overeating, weight gain, hypersomnia, fatigue and leaden paralysis). IMD features are present in ∼30% of patients with Major Depressive Disorder (MDD). By selecting these specific patients, directly targeting inflammation may reduce depressive symptoms.

**Methods:**

and analysis INFLAMED is a double-blind randomized controlled trial. 140 MDD patients with IMD characteristics (MDD with Inventory of Depressive Symptomatology (IDS) ≥ 26, IDS atypical, energy related symptoms ≥6, C-Reactive Protein (CRP) > 1 mg/L) will receive either 400 mg celecoxib per day or matching placebo for a period of 12 weeks. Biological, physical and interview data will be collected after 2, 6 and 12 weeks of starting the intervention. Questionnaires will be sent out bi-weekly during the study period. The main study outcome is the IDS (30-item self-report) total score during 12-week follow-up. Secondary study outcomes include response, remission, adverse side effects, symptom profiles (atypical, energy-related symptoms), fatigue, food craving, sleep, anxiety symptoms, functioning, pain, and optionally, microbiome composition. Explorative analyses will be performed on the role of CRP, IL-6, TNF-α, cholesterol, triglycerides, glucose, BMI, waist and hip circumference.

**Ethics and dissemination:**

This protocol has been approved by the Medical Ethics Review Board of the Amsterdam UMC, location VUmc (2022.0015) on 2-6-2022, as well as by the competent authority in The Netherlands: CCMO, on 3-8-2022.

**Registration details:**

Trail registration numbers NCT05415397, EudraCT 2021-003850-21

## Introduction

1

Research on the effectiveness of antidepressant treatment has shown that all antidepressants are more effective than a placebo, yet approximately only 50–67% of patients with depression achieve remission from these treatments (Cipriani et al., 2018; Gaynes et al., 2009; Otte et al., 2016). Development of more effective treatments requires a better comprehension and targeting of pathophysiological pathways active in patients showing suboptimal treatment response.

Activation of inflammatory pathways in depression is emerging as a promising target for intervention. Inflammation has been shown to be involved in depression-related pathophysiological mechanisms such as monoaminergic neurotransmission alterations, activation of the indoleamine-pyrrole 2,3-dioxygenase (IDO) enzyme degrading tryptophan towards neurotoxic metabolites, glutamate-related neurotoxicity, and Hypothalamic-Pituitary-Adrenal (HPA)-axis dysregulation (Felger and Lotrich, 2013; Miller and Raison, 2016; Obici et al., 2002; Simmons et al., 2020)

Low-grade inflammation has been linked to poorer treatment response and a more chronic course of depression (Arteaga-Henriquez et al., 2019; Vogelzangs et al., 2014). Multiple meta-analyses in subjects with depression or somatic conditions showed the potential clinical effect of anti-inflammatory medication on depressive symptoms (Kappelmann et al., 2018; Kohler-Forsherg et al., 2019; Wittenberg et al., 2020). For instance, the meta-analyses by Köhler-Forsberg and colleagues (2019) showed, by aggregating a series of four small trials totalling 132 subjects, that antidepressant treatment add-on with the non-steroidal anti-inflammatory drugs (NSAIDs) celecoxib achieved a large effect (d = 0.82) in reducing depressive symptoms compared to placebo. Nevertheless, the statistical heterogeneity in meta-analyses was substantial, suggesting underlying clinical differences in the samples examined. Depression is indeed a heterogeneous disorder, with patients expressing diverse and even opposing symptom profiles potentially linked to different underlying mechanisms, thus requiring different specific treatments (Milaneschi et al., 2020).

Indeed, only a subset of depressed patients show low-grade inflammation (Osimo et al., 2019). Emerging evidence indicates that alterations in inflammatory, metabolic, and bioenergetics biological pathways map more consistently to depressive atypical symptoms, reflecting altered energy intake/expenditure balance (overeating, weight gain, hypersomnia, fatigue, and leaden paralysis). We recently proposed a conceptual model of a depression dimension, labelled immuno-metabolic depression (IMD) (Milaneschi et al., 2020), emerging from the clustering of these biological and clinical characteristics. This dimension will now be applied in the stratification and selection of patients to be matched with targeted anti-inflammatory treatment.

More recently, few clinical trials tried to apply a strategy combining selection of specific patients followed by anti-inflammatory treatment. For instance, the MINDEP study selecting MDD patients with C-Reactive Protein (CRP)>1 mg/l showed a positive effect of minocycline augmentation on depression in post-hoc analyses for patients with elevated inflammation [CRP≥3 mg/l] (Nettis et al., 2021). In contrast, the recently completed PREDDICT RCT aimed to stratify by CRP level in their study comparing NSAID celecoxib or placebo as add-on to vortioxetine. Unfortunately, the study was unable to perform planned analyses and unstratified analyses did not show a positive effect of celecoxib (Baune et al., 2021). Thus with these inconsistent results the efficacy of the potential treatment pathway of anti-inflammatory drugs remains unclear. Recently, more trials have started to target the immune system in depression treatment by selecting specific subset of depressed patients, for instance the SIMCODE trial (Otte et al., 2020) and Insight trial (Khandaker et al., 2018).The INFLAMED trial will add to understanding the antidepressant mechanism of anti-inflammatory drugs, by specifically targeting the inflammatory pathway in patients with IMD characteristics.

The INFLAMED study aims to evaluate add-on efficacy of the anti-inflammatory drug celecoxib [400 mg/day] to currently used evidence-based depression treatments (e.g. selective serotonin reuptake inhibitors (SSRI) or serotonin–norepinephrine reuptake inhibitors (SNRI)), for depressed patients with IMD characteristics. By selecting specific patients, the inflammatory pathway to depressive symptoms will be targeted directly and efficiently. The main hypothesis of the current study is that IMD patients receiving treatment as usual (TAU) + celecoxib, will have lower depressive symptom severity over a 12 week period as compared to IMD patients receiving TAU + placebo. This personalized approach has the potential to lead to large health benefits for a substantial proportion of depressed patients.

### Primary objective

1.1

The primary objective of this study is to evaluate whether a 12-week celecoxib treatment added to TAU (defined as SSRI or SNRI pharmacotherapy) is more effective in reducing depressive symptoms as measured with the Inventory of Depressive Symptomatology – self report (IDS 30-item self-report (Rush et al., 2006; Rush et al., 1986; Rush et al., 1996; Rush et al., 2011)) than placebo in patients aged 18–65yr with Major Depressive Disorder (MDD) and IMD characteristics (≥6 IDS atypical, energy related symptoms (Lamers et al., 2013) and circulating CRP>1 mg/l) during 12-week follow up.

### Secondary objectives

1.2

The secondary objective of the study is to examine whether a 12 week celecoxib + TAU is more effective than placebo + TAU in patients aged 18–65 with MDD and IMD characteristics in: reaching treatment response and remission at 12 week follow-up, and improving functioning, lowering fatigue, food craving, and pain at 12 week follow-up.

Additionally, a secondary objective of this study is to better understand how and for whom celecoxib add-on treatment is effective. For this objective, the following biological markers are assessed: CRP, Imterleukine-6 (IL-6), Tumor necrosis factor alpha (TNF-α), cholesterol, triglycerides, glucose, Body Mass Index (BMI), waist and hip circumference. Explorative analyses will be performed on the mediating/moderating role of these markers. These analyses will provide suggestions on whether a potential treatment effect is achieved through modulation of immune-metabolic markers, hypothesized to be at the core of IMD pathophysiology.

## Methods

2

This protocol was prepared following Standard Protocol Items: Recommendations for Interventional Trials (SPIRIT) guidelines (Chan et al., 2013). The full checklist can be found in Supplement B.

### Study design and sample

2.1

In total, 140 depressed patients with IMD characteristics (e.g. ≥6 IDS atypical, energy related symptoms and circulating CRP>1 mg/L) and undergoing TAU in primary or secondary care will be randomized (1:1) to celecoxib (400 mg/d) or matched placebo for 12 weeks in a parallel group, superiority framework RCT.

The study will be a monocenter study from the Amsterdam University Medical Centres, location VUmc, department of Psychiatry. Recruitment of participants will be done through a dedicated study website. Local mental health clinics will be approached to refer potential participants to the study website. The study website contains the Patient Information Folder (PIF) and the online screening questionnaire.

### Intervention

2.2

Patients in this study will receive either an add-on placebo or celecoxib (400 mg/d) in an oral dose of 200 mg per capsule, to be taken twice daily. Celecoxib was chosen as the study medication for four reasons. Firstly, celecoxib is an already available drug since 1999, commonly prescribed for arthritis. Secondly, celecoxib is an affordable generic, with costs less than one euro per capsule. Thirdly, celecoxib has shown most promising preliminary results in depression (Kohler-Forsherg et al., 2019). Finally, celecoxib has a safety profile superior to other NSAIDs (Nurmohamed, 2017).

#### Choice of dosage

2.2.1

A dosage of 400 mg/day is the oral dosage indicated for the managing of acute pain and previously adopted by all RCT testing the efficacy of celecoxib as add-on to antidepressant treatment in patients with MDD (Kohler-Forsherg et al., 2019; Baune et al., 2021). These studies reported no major adverse events for celecoxib add-on of 400 mg/day. The selected dosage will ensure adequate safety for the study subjects and the possibility to compare results across different studies.

### Study procedure

2.3

To ensure safe participation and to answer the research questions properly, potential participants will undergo an extensive screener procedure. Full in- and exclusion criteria can be found in Table 1.

**Table 1 tbl1:** In- and exclusion criteria for the INFLAMED trial.

Inclusion	Exclusion
➢ Age 18–65 years	➢ Contraindications for celecoxib (history of: peptic ulcers, gastrointestinal bleeding, ischemic heart disease, stroke, heart failure, allergic reactions to aspirin/NSAIDs/coxibs; impaired kidney function (creatinine clearance < 30 ml/min); impaired liver function (ALT > 2x upper limit of normal [ULT]))
➢ DSM-5 diagnosis of MDD confirmed with clinical interview (MINI)	➢ Electroconvulsive therapy (ECT) in the past 3 months
➢ Currently using an SSRI or SNRI; subjects should be on the current medication for at least 4 weeks	➢ Being on antidepressants other than SSRIs or SNRIs or being on other psychotropic drugs
➢ IDS score ≥26 and a score ≥6 on atypical, energy-related symptoms scale from IDS ➢ CRP>1 mg/L	➢ Starting other evidence-based non-pharmacological intervention for depression (e.g. psychotherapy) in the 4 weeks before randomization. Clinically overt alcohol/drug dependence or other primary psychiatric diagnoses (schizophrenia, schizoaffective, Obsessive-compulsive disorder (OCD), or bipolar disorder)
➢ A female participant is eligible to participate if one of the following conditions applies: - She is not a woman of child bearing potential (WOCBP) - She is a WOCBP and is not pregnant or breastfeeding. Furthermore, she agrees to use, or is already using, a contraceptive method during the intervention period and up to 1 month after the intervention. A WOCBP must have a negative highly sensitive pregnancy test before the first dose of the study intervention.	➢ Chronic use of anti-inflammatory drugs and corticosteroids ➢ Current use of anticoagulants
➢ Signed informed consent	➢ Not speaking Dutch

### Eligibility assessment

2.4

Potential participants will enrol through the study website by filling in the IDS and their age as the first steps of screening, after having read the PIF and online consent for screening.

If participants are eligible for the next step (18–65yr, IDS ≥26, atypical, energy related symptoms ≥6), a video-interview will be planned with a trained researcher. In this interview, participants will have the opportunity to ask questions, before signing informed consent to collect data for further screening. After this, participants undergo the interview for the in- and exclusion criteria mentioned in Table 1, including a diagnostic interview to asses for current DSM-5 diagnosis MDD (American Psychiatric Association, 2013).

If still deemed eligible after the interview and after having returned the signed informed consent to researchers, participants will receive a fingerprick-kit for a blood draw at home (or venepuncture at study site if preferred). If a participant has low-grade inflammation (CRP>1) on this test and if there are no signs of liver problems (ALT ≤ 2x upper limit of normal [ULT]) or kidney problems (creatinine clearance ≥30 ml/min), they can be enrolled in the study. The study flow is displayed in Fig. 1.

**Fig. 1 fig1:**
[figure not shown]
Flow chart of inclusion procedures for the INFLAMED study. IDS: Inventory of Depressive Symptomatology, MDD: Major Depressive Disorder, CRP: C reactive protein.

#### Concomitant care during the trial

2.4.1

Medication that is contraindicated with celecoxib is not permitted (i.e. anticoagulants). Chronic use of other psychotropic medications, NSAIDS or corticosteroids, are also not permitted. Exceptions are for example made for low dosages psychotropic medications if needed for sleep (for instance, low-dose of mirtazapine, amitriptyline or quetiapine).

Psychotherapy (in any form) is not permitted to start in the 4 weeks before randomization. Participants are permitted to be in therapy for longer than four weeks, or to start a new psychotherapy during study participation. Changes in treatment are recorded during the course of the study.

### Baseline data collection

2.5

All positively screened participants will be invited for the baseline measure at the study site. Participants have again the opportunity to ask questions about participation, before signing informed consent for study participation. After informed consent is signed, participants are randomized to the celecoxib or placebo group. Participants will then undergo a (sober) blood draw, physical measurements and fill out questionnaires. Finally, at the end of this baseline measurement, participants will receive the study medication for the full duration of the trial from the hospital pharmacy, including clear instructions on usage.

### Follow-up measures

2.6

Follow-up measures will take place every two weeks after the baseline measures (see Fig. 1), up to the final assessment after twelve weeks. The measures at week 4, 8 and 10 will be online questionnaires. At week 2 and 6 participants are invited to the study site for a blood draw, interview, physical measurements and questionnaires. At these measurements, potential side effects, blood pressure and creatinine levels will be monitored. In case of adverse reaction to the study medication, participants will be pulled out.

The final visit is at week 12. This includes a blood draw, interview, physical measurements and questionnaires, as well as an evaluation of the study by participants, adherence to the protocol, returning any leftover medication and a drug count. Any travel or parking costs made by the participants during the study will be reimbursed. Participants will receive a gift card of €30 for every visit to the research centre.

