### Sample size

2.8

In order to properly calibrate the sample size calculation for this longitudinal treatment study we estimated an expected effect size from similar anti-inflammatory add-on published trials. A previous meta-analysis (Köhler‐Forsberg et al., 2019) including 4 RCTs showed a significant effect of celecoxib add-on, as compared to placebo, to standard first line (SSRI/SNRI) antidepressant treatment with a pooled standardized mean difference (SMD) of −0.82 [95%CI: −1.17, −0.46]. We calculated a standardized effect size from the recent PREDDICT trial (Baune et al., 2021) showing no significant difference between placebo versus celecoxib add-on to vortioxetine. From this trial, the differences in means in the two treatment groups at the end of the treatment were standardized using baseline standard deviations, obtaining a SMD of 0.30 [95%CI: −0.06, 0.66]. We pooled the effect sizes for all the 5 trials mentioned above using a random effect meta-analysis (see forest plot below). The pooled SMD was −0.52 [95%CI: −1.05, 0.01] which we used in subsequent power calculations.

Power calculations were performed with the “powerlmm” package (Power Calculations for Longitudinal Multilevel Models, v. 0.4.0) in R v4.0.0 (R Project for Statistical Computing), which is based on the analytical model described in Galbraith and Marschner (2002). We considered a study design with 6 follow-up repeated assessments of depressive symptoms with an ICC of 0.5 and an overall SMD of −0.52 (see Fig. 2) between treatment groups (1:1 ratio) across the follow-ups. We additionally modelled attrition based on the recent results of the PREDDICT trial (Baune et al., 2021), reporting drop-outs of 16% in the placebo add-on group and 12% in the celecoxib add-on at the end of the treatment. Under these assumptions, a sample size of 140 subjects allows to detect a significant (α = 0.05) treatment-by-time interaction effect with 83% statistical power.

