### Data analysis

2.10

Analyses will be performed following an Intention-To-Treat principle: all participants will be included in the analysis according to their allocated treatment group at randomization. The primary outcome will be analysed using data from all post-randomization time points: 2-week, 4-week, 6-week, 8-week, 10-week and 12-week assessments. Given the correlation between repeated measures within subjects, linear mixed models will be used including a random intercept at subject level. Linear mixed models are able to handle missing data using maximum likelihood estimation. In the primary analysis, fixed effects will consist of treatment, a linear effect of time, and a treatment-by-time interaction. In secondary analyses, time will be dummy-coded and all two-way interactions between treatment and time dummies will be entered in the model to allow the estimation of group means at each time point. Estimates will be adjusted for the baseline IDS scores. Standardized effect sizes will be computed by dividing the estimated mean treatment group difference (across the overall follow-up and at each follow-up assessment) by the SD of the baseline outcome. The statistical significance threshold will be set at α = 0.05, two-sided. Analysis for the secondary outcomes will follow the same approach as the primary outcomes. Descriptive statistics will be calculated for adverse events. All statistical analyses will be performed using R or SPSS.

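### The adverse-reaction rule, read plainly, ends IDS collection for a treatment-related reason and leaves the intention-to-treat analysis resting on an avoidable missing-at-random assumption

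*Protocol article*

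**What the plan says.** The rule is in the protocol article, section 2.6 (Follow-up measures): "In case of adverse reaction to the study medication, participants will be pulled out". It follows directly on the safety checks at the week 2 and week 6 site visits: "At these measurements, potential side effects, blood pressure and creatinine levels will be monitored". The same section says of the remaining interim assessments: "The measures at week 4, 8 and 10 will be online questionnaires". No severity threshold is attached to the rule. Nothing in the article separates stopping the capsules from leaving follow-up, and nothing says that the IDS continues afterwards. Withdrawal of consent is a separate route out (Consent section).

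Section 2.10 (Data analysis) declares intention-to-treat: "all participants will be included in the analysis according to their allocated treatment group at randomization". The primary outcome uses all six assessments from week 2 to week 12. In the primary model "fixed effects will consist of treatment, a linear effect of time, and a treatment-by-time interaction", with adjustment for baseline IDS and a random intercept per subject. On gaps in the data it says: "Linear mixed models are able to handle missing data using maximum likelihood estimation".

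**The concern.** The subject of the sentence is the participant, not the capsules, and it stands in the section on follow-up. Its natural reading is removal from the trial. That is an exit imposed by the protocol, triggered by the study drug, in a trial whose primary analysis is meant to describe all randomized participants as allocated.

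Maximum likelihood does not recover that target by itself. For a participant whose scores stop, the model in effect extrapolates from those still followed in the same arm, most of whom are still on treatment. If the missing scores follow that pattern given arm, baseline IDS and the scores already seen, the estimate is valid for the effect had treatment continued. It equals the intention-to-treat effect only if scores after stopping would have looked the same. Nobody could check this, because those scores would not exist, and an analysis plan can vary the assumption but cannot supply the data. The loss is avoidable: the IDS is self-report, and half of its follow-up assessments are already online.

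**Working it through.** **Scores lost (from the schedule).** Follow-ups are at weeks 2, 4, 6, 8, 10 and 12.
- Out at week 2, that score kept: weeks 4, 6, 8, 10 and 12 are lost, 5 of 6. Three of these (4, 8, 10) are online.
- Out at week 6, that score kept: weeks 8, 10 and 12 are lost, 3 of 6. Two of these (8, 10) are online.

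**Inputs from the protocol.** 70 per arm (Randomization); "6 follow-up repeated assessments of depressive symptoms with an ICC of 0.5" and a standardized difference of 0.52 (Sample size); the model in Data analysis.

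**Assumptions, not in the protocol.** A fraction *p* is pulled out in each arm, half at week 2 and half at week 6, with *p* = 4%, 8% or 12%. Total SD is 1. The on-drug difference is 0.52 × week/12. After stopping, the celecoxib mean returns to the placebo mean from the next visit. Effects are given as positive benefits.

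**Check of the set-up.** With six complete visits numbered 1 to 6, the centred sum of squares is 17.5. The SE of the interaction over 12 weeks (6 visit steps) is 6 × √(2 × 0.5/(70 × 17.5)) = 0.171. With all-cause dropout of 12% on celecoxib and 16% on placebo spread evenly, the SE is about 0.18, and power is Φ(0.52/0.18 − 1.96) = 82%, close to the stated 83%. This shows only that the set-up is reasonable. Other readings of the stated inputs give 81% (two-sample comparison of completers) or 93–95% (a random-intercept slope test in which the full 0.52 builds up between the first and last assessments analysed).

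**Post-stop scores not collected.** The model returns 0.520, the on-drug effect, at every *p*.

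**Post-stop scores collected and included.** The fractions off drug at visits 1 to 6 are 0, *p*/2, *p*/2, *p*, *p*, *p*. The benefit lost at visit *j* is 0.52 × *j*/6 times that fraction. The interaction falls by

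(6/17.5) × (0.52/6) × *p* × [−1.5×2×0.5 − 0.5×3×0.5 + 0.5×4 + 1.5×5 + 2.5×6] = (0.52/17.5) × 22.25 × *p* = 0.661*p*.

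| *p* per arm | Not collected | Included | Overstatement (SD per 12 weeks) | Power, not collected | Power, included |
|---|---|---|---|---|---|
| 4% | 0.520 | 0.494 | 0.026 | 84.7% | 82.1% |
| 8% | 0.520 | 0.467 | 0.053 | 83.5% | 77.8% |
| 12% | 0.520 | 0.441 | 0.079 | 82.1% | 72.9% |

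The power columns assume no other attrition. At 4% the gap is 0.026/0.174 = 0.15 of the standard error that applies when post-stop scores are absent.

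**Sensitivity.**
- Half the benefit persists: the gaps halve. All persists: they are zero.
- All out at week 2: 0.024, 0.048, 0.071. All out at week 6: 0.029, 0.058, 0.087.
- Constant 0.52 effect from week 2: 0.025, 0.050, 0.075. The on-drug interaction is then zero, so the gap cannot be expressed as a percentage of it.
- Sign reversal: 4% of celecoxib and 12% of placebo pulled out, benefit lost, and both arms also 0.5 SD worse after stopping. Worsening adds 0.5 × (6/17.5) × 3.5 × (0.12 − 0.04) = 0.048, and lost benefit removes 0.661 × 0.04 = 0.026. The interaction with scores included is 0.542, so 0.520 understates it by 0.022.

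**The case against.** The strongest reply is that this is one short line in a condensed article. A full protocol (version 1.6) exists and is not shown, and procedures after stopping medication are commonly left to it. The sentence follows the safety checks and concerns a reaction to the medication, so it may mean off the capsules only. The promise in Data analysis to use every post-randomization time point fits that reading. This stands in part: the capsules-only reading is possible. But the article states a rule about participants rather than staying silent. If capsules-only is meant, the same one-sentence edit says so.

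The size also rests entirely on assumption. The top rate of 12% equals the all-cause celecoxib dropout cited under Sample size, so every dropout would have to be an adverse-reaction exit. Choice of dosage reports no major adverse events at this dose in earlier trials, which points to the low end without excluding minor reactions. These points stand.

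A reader might infer three stronger things that the documents do not support:
- That data are thrown away. On the plain reading later scores are never collected, and earlier ones stay in the analysis.
- That the primary model is faulty for lacking an adverse-reaction term. Such a term would be a post-randomization covariate and does not belong there.
- That the rule contradicts intention-to-treat. Participants remain in their allocated arm; the principle is weakened, not broken.

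The section on concomitant care says "Changes in treatment are recorded during the course of the study", which might be set against the pull-out rule. That line concerns other treatments, and little follows from it.

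**Conclusion.** The point holds as a wording fault with a real consequence for the primary analysis. Followed as written, the rule stops the IDS for a treatment-related reason, and the estimate then tends towards the effect had treatment continued. With 4–12% pulled out per arm, an effect growing linearly to 0.52 SD and full loss of benefit after stopping, the interaction is overstated by 0.03–0.08 SD per 12 weeks, even with equal withdrawal in the two arms. It might be tempting to conclude that the trial is biased in favour of celecoxib. The documents do not support that: they give no adverse-reaction rate, the gap is zero if benefit persists, and other assumptions reverse its sign. The change is worth making because the missingness is avoidable, not because a particular bias has been shown.

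**What to change.** Reword the sentence so that an adverse reaction stops study medication only. State that the IDS, the other questionnaires (online if visits are declined) and safety follow-up continue to week 12 unless consent is withdrawn. Record the date and reason for stopping, and include post-stop scores in the primary intention-to-treat analysis. The decision on when to stop the medication does not change.

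The cost is a text change in the protocol and patient information, and a few extra participant contacts using assessments already scheduled. If benefit is lost after stopping, the estimated effect will be smaller and power for the interaction somewhat lower: about 3 points at 4% and 9 points at 12% under the assumptions above. The sponsor should know this against the planned 83%, but it is no reason to leave the scores uncollected.
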